### Eligibility Criteria

In the present investigation, we arbitrarily decided not to include children aged less than 1 year of age because the functional capacity of the kidney, including glomerular filtration rate and renal concentration ability, as well as the efficiency to excrete sodium load is lower in infants than in older children [30-33]. Hence, the study population will be male and female children and adolescents aged between 1 and 14 years old whose post-operative p-Na^+ ^are within the normal range (local reference range: 135 - 147 mmol/L). Children and adolescents undergoing emergency intervention for treatment of acute appendicitis either as an open or laparoscopic procedure will be considered to be potentially eligible. To qualify for randomization, the participants are required to have a complicated appendicitis, i.e., gangrenous or perforated, either with generalized or localized peritonitis of such a degree that the surgeon considers oral feeding unsuitable for at least 24 h following the surgery. Consequently, the randomization will be performed post-operatively and on the basis of intra-operative findings.

We infer that in our study population, the prescription of parenteral fluid therapy for the immediate 24 h post-operative period might be justified, and that by delaying oral fluid therapy intake, in any particular case, will do no harm to the patient.

The exclusion criteria will be any clinical condition, such as renal disease, acute or chronic lung inflammation, pituitary or hypothalamic disease, and adrenal insufficiency that eventually can lead to electrolyte and water imbalance. In addition, any patient whose p-Na^+ ^is < 130 mmol/L after the initiation of parenteral maintenance fluid therapy, will be withdrawn from the study and treated accordingly at the discretion of the anesthesiologist responsible for the patient's care [34].

Whenever the occurrence of vomiting is reported or if the patient complains of symptoms attributable to symptomatic hyonatremia such as nausea, malaise, headache, restlessness, drowsiness, or decreased consciousness, p-Na^+ ^will be immediately controlled and the event clearly documented in the medical record.

During the first 24 h post-operatively, the administration of extra fluid besides the study maintenance fluid therapy, will be not permitted with the exception of fluid administered with medication or to maintain patency of peripheral intravenous catheters.

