### Analysis population

Three analysis populations will be used in this study. The "intention to treat" population will consist of all subjects who have been randomized and have received one of three parenteral maintenance fluid therapies previously mentioned. The analysis will be conducted in all "intention to treat" patients who had no protocol violation(s) or deviation(s).

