Since prescription of intravenous fluid therapy given at full maintenance rate may be potentially dangerous when renal water excretion is limited by ADH excess, parenteral fluid therapy will be given at a lower rate than the recommended average maintenance rate [8]. Consequently, and, in accordance with our local care guidelines for parenteral fluid therapy following surgical procedures, ~¾ of the average maintenance rate will be prescribed for the first 24 h post-operatively, i.e., from T_0 _to T_24_. Table 1 relates body weight to ~¾ of the average maintenance allowances for hourly periods.

**Table 1 T1:** 24 h post-operative fluid volume at ~¾ of average maintenance rate according to Holliday-Segar formula.

Weight (kg)	ml/kg/24 h
10	80
11	76
12	73
13	71
14	69
15	67
16	65
17	64
18	62
19	61
20	60
22	56
24	53
26	51
28	49
30	47
35	43
40	40
45	38
50	36
55	35
60	33
65	32
70	31

Ongoing post-operative losses, e.g., nasogastric drainage following abdominal surgery, will be replaced ml for ml with Ringer's lactate solution.

Below, we describe an example of the likely change in p-Na^+ ^that would result at T_24 _in a previously healthy 10 year-old-boy who met the inclusion criteria to participate in the study. We presuppose that our hypothetical case has been randomized to be treated with 0.23% salt solution in 5% glucose. We assume that, similar to patients we expect will participate in our study, his kidneys are capable of generating concentrated urine in response to non-osmotic stimulated ADH activity. Since in the immediate post-operative period a child with intact urinary concentration ability may achieve urine osmolality of more than 700 mosmol/kg H_2_O as a result of elevated ADH levels [38], in our example we arbitrarily set the urine osmolality at 900 mosmol/kg H_2_O.

In this hypothetical case we take into account all the patient's inputs during the 24 h period following surgery, i.e., total volume of water, Na^+^, K^+^, and Cl^-^. Each element is analyzed separately and it is supposed that all the infused Na^+^, K^+^, and Cl^- ^represent the renal solute load that eventually will be excreted in the urine [39]. Thus, one mmol of each of these elements equals one mosmol. Since glucose is metabolized to carbon dioxide and water, it does not contribute to renal solute load in our example. Similarly, in solutions containing acetate, this anion is metabolized in the liver and does not contribute to renal solute load.

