It should be noted that, for the sake of simplicity, we have chosen to take for granted that in this hypothetical case the urine osmolality would be fixed during the 24 h period following surgery. This, and the fact we only consider the patient's input of water and electrolyte, might confine the accuracy in our predicting p-Na^+ ^at T_24_. Therefore, in our study, the patient's expected p-Na^+ ^at T_24 _will be calculated by computing actual water and electrolyte balance during the first 24 h post-operatively as follows:

where the subscripts _f _and _i _represents final (T_24_) and initial (T_0_) p-Na^+^, respectively; Δ (Na^+ ^+ K^+^) represents cation input (infused) minus cation output (urinary excretion); TBW represents the estimated initial total body water and ΔTBW describes the water infused minus water excreted, respectively.

In our study we will analyze, by applying the same approach as described in our hypothetical case, whether p-Na^+ ^at T_24 _can be correctly estimated by using the patient's immediate postoperative urine osmolality value. The estimated p-Na^+ ^obtained by this method and by means of water and electrolyte balance will be plotted against the patient's actual p-Na^+ ^measured at T_24 _for assessing agreement between methods [40].

Twenty-four hour insensible water losses in each participant will be calculated as follows:

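### Loss replacement with Ringer's lactate is ordered in one section and excluded by another for the same 24 h, and the cation balance counts only urine as output

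*Protocol article*

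**What the plan says.** **Restriction on fluid (Eligibility Criteria, last paragraph).** For the first 24 h after surgery, "the administration of extra fluid besides the study maintenance fluid therapy, will be not permitted with the exception of fluid administered with medication". The sentence then adds a second exception, "or to maintain patency of peripheral intravenous catheters". These are the only two exceptions.

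**Fluid regimen (Parenteral Fluid Therapy, post-operative fluid management).** About three quarters "of the average maintenance rate will be prescribed for the first 24 h post-operatively", defined there as T0 to T24. Directly after the table of 24 h volumes comes the instruction: "Ongoing post-operative losses, e.g., nasogastric drainage following abdominal surgery, will be replaced ml for ml" with Ringer's lactate.

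**Analysis set (Analysis population).** The analysis covers "patients who had no protocol violation(s) or deviation(s").

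**Balance (Parenteral Fluid Therapy).** Each child's expected p-Na+ at T24 "will be calculated by computing actual water and electrolyte balance during the first 24 h post-operatively". The change in sodium plus potassium "represents cation input (infused) minus cation output (urinary excretion"). The water term is infused minus excreted water. The introduction to the worked example says it takes in the patient's "inputs during the 24 h period following surgery, i.e., total volume of water", together with sodium, potassium and chloride. Clinical and Laboratory Assessment describes electrolyte output measurement for urine only.

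**The concern.** Both fluid rules are mandatory and cover the same period. Read literally, the Eligibility Criteria leave a draining child's loss unreplaced, while the regimen section replaces it in full. Staff cannot comply with both.

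Two things follow. First, because the analysis is limited to children without violations or deviations, someone must decide whether ordered replacement fluid is a deviation, and the text points both ways. Second, the balance calculation has no place for the cations that leave with the drained fluid. Water and electrolyte balance is the stated secondary aim, and the p-Na+ predicted from it is to be compared with the measured T24 value. An error in the balance rule would then appear as poor agreement between methods in exactly those children who had losses.

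**Working it through.** **1. Do the two fluid rules overlap?**

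| | Eligibility Criteria | Parenteral Fluid Therapy |
|---|---|---|
| Window | first 24 h after surgery | T0 to T24 |
| Fluid beyond maintenance | barred | Ringer's lactate, ml for ml, for ongoing losses |
| Allowed by exception | fluid with medication; catheter patency | not addressed |

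The ban cannot be read as covering only extra maintenance fluid. Neither listed exception is maintenance fluid, so neither would need listing on that reading. The ban reaches all other fluid, and replacement fluid is not exempted.

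**2. Reproduce the article's 30 kg example.** Table 1 gives 47 ml/kg, and 47 × 30 = 1410 ml, as stated. For the 0.23% solution, 1.41 × (40 + 20 + 60) = 169.2 mosmol, as stated.

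**3. Maintenance cations infused (Na + K, compositions from Study Design).**
- 0.23%: 1.41 × (40 + 20) = 84.6 mmol
- 0.40%: 1.41 × 70 = 98.7 mmol
- 0.81%: 1.41 × (140 + 4) = 203.0 mmol

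**4. Cations without a matching output.** If replacement fluid is counted as infused and output is urine only, the balance is too high by lost volume × Na + K concentration of the lost fluid. The article gives neither figure. Assuming 30 to 140 mmol/L, 0.1 L gives 3 to 14 mmol.

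| Arm | 3 mmol as share | 14 mmol as share |
|---|---|---|
| 0.23% | 3/84.6 = 3.5% | 14/84.6 = 16.5% |
| 0.40% | 3/98.7 = 3.0% | 14/98.7 = 14.2% |
| 0.81% | 3/203.0 = 1.5% | 14/203.0 = 6.9% |

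**5. Why the effect on predicted p-Na+ cannot be fixed.** The equation is not shown in the text at hand. Assume (140 × 18 + cation change) ÷ (18 + water change), with total body water 18 L and p-Na+ 140 mmol/L from the example, everything other than the loss and its replacement in balance, and Ringer's lactate at an assumed 135 mmol/L of Na + K. For 0.1 L lost and replaced (13.5 mmol in):
- Correct accounting: (2520 + 13.5 − 3)/18 = 140.58, or (2520 + 13.5 − 14)/18 = 139.97.
- Lost cations omitted, lost water counted: 2533.5/18 = 140.75, an error of +0.17 to +0.78 mmol/L.
- Lost cations and lost water both omitted: 2533.5/18.1 = 139.97, an error of −0.61 to 0.00 mmol/L.

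The direction thus depends on how water is handled. For scale, the article's own predictions for the three arms (136.5, 136.4 and 138.2) span 1.8 mmol/L.

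**6. If treated children were dropped as deviators.** The stated 17 per arm reproduces: a two-sided two-sample t-test with difference 5, SD 5, alpha 0.05 and 80% power needs 16.7, and 17 gives 80.7%. With an assumed 10%, 20% or 30% dropped (15.3, 13.6 or 11.9 per arm), power would be about 76%, 71% or 64%. The article gives no such rate and does not say these children would be dropped.

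**The case against.** The strongest reply is that the restriction closes the eligibility section, while the replacement order is a specific instruction in the section that governs treatment. A sensible reader would take replacement as part of the regimen and the ban as aimed at discretionary fluid. On that view one clause is missing and fluid that the protocol orders is no deviation. That is probably what the authors intended, but the wording does not say it: the ban names the study maintenance fluid and then lists what else is allowed.

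On analysis, deviations are commonly classified in the SAP, which is not shown. This stands: exclusion is possible, not stated, and the power figures are illustration only.

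On the balance, only the legend of the equation survives, and the error arises only if replacement is counted as infused. The worked example uses the maintenance volume alone, so it does not show how replacement would be handled. Losses replaced ml for ml might be left out on both sides, which would leave only the difference in composition between lost and replacement fluid. These points rightly keep the size and direction open. But leaving losses out on both sides is not in the text, whereas infused minus urinary excretion is.

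Finally, shares of infused cations look larger than the resulting change in p-Na+. That is fair: under the assumptions in step 5 the change per 100 ml is below 1 mmol/L.

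**Conclusion.** The concern holds. The treatment rules conflict as written: one excludes, and the other orders, replacement of losses in the same 24 h. This rests on the text alone. The balance rule is also wrong as written for a child whose losses are replaced, on the condition that replacement counts as infused, which is the plain meaning of the term.

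The number of children affected is unknown. The unmatched amount is 3 to 14 mmol per 100 ml lost, at an assumed 30 to 140 mmol/L, or 1.5% to 16.5% of maintenance cations in the 30 kg example. The effect on predicted p-Na+ is not settled in size or sign. The balance definition does not touch the primary outcome, which is measured p-Na+ at T24. The point should be fixed, but it does not undermine the trial.

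**What to change.** 1. In Eligibility Criteria, add replacement of measured ongoing losses with Ringer's lactate to the permitted fluids, and state that it is protocol treatment and not a deviation.
2. In the balance definition under Parenteral Fluid Therapy, define water and cation output as urine plus measured non-urinary losses, and count replacement fluid as input.

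The cost is one added clause and one clarified definition. The lost volume has to be measured anyway to replace it ml for ml. The only extra burden is that the cation content of the lost fluid must be measured or assumed; if assumed, the value should be fixed in advance. The article says that enrolment follows publication and that comments are expected to improve the protocol, so both changes can be made before the first child is randomized.

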### Analysis population

Three analysis populations will be used in this study. The "intention to treat" population will consist of all subjects who have been randomized and have received one of three parenteral maintenance fluid therapies previously mentioned. The analysis will be conducted in all "intention to treat" patients who had no protocol violation(s) or deviation(s).

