### Patient Randomization

The study population will be allocated to each of the intervention groups using randomization in blocks. Block size will be kept secret to all study related personnel. Participants will be numbered sequentially. It is expected that after the randomization there will be no differences in the clinical or biochemical characteristics among different treatment groups at the start of post-operative parenteral fluid therapy. After randomization, the anesthetist and the clinical team will be informed by the surgeon to which fluid regimen arm the patient has been allocated.

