#### Sample size calculation

The expected sample size required in our study is based on the calculation for equality applied to the primary outcome variable p-Na^+^, measured at T_24 _as mmol/L.

In the previous section we estimated that the largest expected fall in p-Na^+ ^in our illustrative case would be 3.6 mmol/L. Consequently, if we apply this figure to a patient whose p-Na^+ ^at T_0 _is 135 mmol/L, the expected p-Na^+ ^at T_24 _after giving 0.4% sodium chloride would be 131.4 mmol/L, a plasma level which may not have clinical significance [27]. However, we are compelled to speculate that this figure may not be exact because in our illustrative case we dealt with hypothetical data that may not necessary mirror the clinical setting. Hence, our estimate has to be verified by means of water and electrolyte balance measurement *in vivo*. Taken this uncertainty into account, we arbitrarily decided that the equality margin will be set at 5 mmol/L. This value will capture our estimate, but, most importantly, in patients whose p-Na^+ ^at T_0 _is 135 mmol/L, it would allow us to identify those patients who are at risk for developing hyponatremia of potential clinical significance [27]. Thus, a difference between treatment groups greater than this margin will be considered as clinically relevant. Consequently, a difference smaller than 5 mmol/L will be considered as clinically less relevant. Sample size was calculated assuming a standard deviation (SD) of 5 mmol/L, a significance level of 0.05, and a power of 80% to detect a difference larger than the equality margin of 5 mmol/L. Hence, the number of patients per study arm needed to fulfill the power goal of the study will be 17 patients.

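### As printed, the primary comparison is run in a deviation-free subset rather than in the randomised-and-treated set that the protocol itself defines

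*Protocol article*

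**What the plan says.** All references are to the protocol article.

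- *Analysis population* opens with "Three analysis populations will be used in this study". It names one, intention to treat, and defines it as "all subjects who have been randomized and have received one of three parenteral maintenance fluid therapies previously mentioned". This is a modified intention-to-treat set, because receipt of fluid is required. The section then says where the analysis is run: in the intention-to-treat "patients who had no protocol violation(s) or deviation(s". No third population is described.
- *Data analysis* specifies ANCOVA with treatment as fixed factor and baseline as covariate. It names no analysis set. It leaves the handling of missing data to the statistical analysis plan.
- *Sample size calculation* identifies the "primary outcome variable p-Na^+^, measured at T_24 _as mmol/L" and arrives at 17 children per arm. It mentions no allowance for excluded children.
- *Patient Randomization* says that after allocation "the anesthetist and the clinical team will be informed by the surgeon to which fluid regimen arm the patient has been allocated".
- *Eligibility Criteria* says that in the first 24 h "the administration of extra fluid besides the study maintenance fluid therapy, will be not permitted", with exceptions for fluid given with medication and for keeping catheters open. It also says that "any patient whose p-Na^+ ^is < 130 mmol/L after the initiation of parenteral maintenance fluid therapy, will be withdrawn from the study".

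**The concern.** Randomisation protects the comparison only among children kept in the analysis irrespective of what happens afterwards. A protocol deviation happens after allocation. Here the team knows the arm and also sees sodium at 6 h and 12 h, with further sampling at the anaesthetist's discretion if it is falling. Deviations could therefore depend on both the arm and the child's course. The documents do not show that they will, but nothing in the design prevents it.

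Two features make the choice of set matter more than usual. The stated aim is whether the fluids are equally effective, so a bias towards no difference favours one of the possible conclusions. The exclusion also has no threshold: any violation or deviation removes the child, however small, and no adjudication rule is given. What counts as a deviation is itself unsettled. *Eligibility Criteria* forbids extra fluid apart from two exceptions, while *Parenteral Fluid Therapy* provides for replacement of ongoing losses. A child given such replacement could be classed either way, so the two statements must be reconciled before a deviation-free set can be formed.

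**Working it through.** **1. Which set does the text assign to the primary analysis?**

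- Sets announced: three. Sets named and defined: one. Sets described without a name: one, the deviation-free subset. Sets not described: one.
- Statements that assign an analysis to a set: one, the last sentence of *Analysis population*, and it assigns the deviation-free subset.
- *Data analysis* and *Sample size calculation* contain no competing assignment.

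Followed literally, the ANCOVA is run in the deviation-free subset.

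**2. The plan's own sample size.** Inputs from *Sample size calculation* and *Data analysis*: difference 5 mmol/L, SD 5 mmol/L, two-sided alpha 0.05, power 80%.

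- Normal approximation: n = 2 × (1.960 + 0.842)² × (5/5)² = 15.7, rounded up to 16 per arm.
- Two-sample t-test (noncentral t): 16.7, rounded up to 17 per arm, with power 0.807.

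The stated 17 reproduces. It is background to this point and is not itself in error.

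**3. Precision lost if children are excluded from 17 per arm.** Same t-test, effect size 5/5 = 1. One child is 1/17 = 6% of an arm.

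| Analysed per arm | Power |
|---|---|
| 17 | 0.807 |
| 15 | 0.753 |
| 13 | 0.687 |

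To keep 17 evaluable per arm under assumed exclusion rates, the number randomised per arm would be 17/0.9 = 18.9, so 19 (10% excluded); 17/0.8 = 21.3, so 22 (20%); 17/0.7 = 24.3, so 25 (30%). These rates are assumptions, as the document gives none. Baseline adjustment by ANCOVA may make actual power higher than the table shows.

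**4. Direction of bias, one conditional illustration.** The document does not say whether a child withdrawn for sodium below 130 mmol/L counts as having deviated or stays in the analysis. Suppose such children leave the analysed set, and suppose 24 h values are normal with mean m and SD s. The mean of those who remain is m + s × φ(a)/(1 − Φ(a)), with a = (130 − m)/s.

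*Means 136.4 and 138.2* (the worked-example values for the 0.40% and 0.81% solutions, taken here as arm means), s = 5:

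- m = 136.4: a = −1.28; 136.4 + 5 × 0.1758/0.8997 = 137.38; about 10% removed.
- m = 138.2: a = −1.64; 138.2 + 5 × 0.1040/0.9495 = 138.75; about 5% removed.
- The difference goes from 1.8 to 1.37 mmol/L (to 1.70 with s = 3).

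*Means 133.2 and 138.2* (the lower mean is assumed, so that the true difference equals the 5 mmol/L margin), s = 5:

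- m = 133.2: a = −0.64; 133.2 + 5 × 0.3251/0.7389 = 135.40; about 26% removed.
- The difference goes from 5.0 to 138.75 − 135.40 = 3.35 mmol/L (to 4.24 with s = 3).

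This pattern narrows the difference because the lower arm loses more of its low values. Other patterns could widen it: for example, if low-sodium children in the higher-sodium arm were given extra fluid and excluded for that reason.

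**The case against.** The strongest reply is that the last sentence of *Analysis population* is a drafting lapse. The section says three populations will be used and takes the trouble to define the intention-to-treat set. A set that is defined and announced for use is not plainly discarded, and the sentence may be a per-protocol definition that lost its label. The promise to replace missing data also suggests that incomplete children are kept, and full detail is left to an analysis plan that is not shown. This stands as far as intent goes: a reader might infer that no analysis of all treated children was ever planned, and the document does not establish that. It does not rescue the wording, because the sentence is a positive statement about where the analysis is run, and nothing else in the article corrects it.

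A reader might also infer that a per-protocol set is being passed off as intention to treat. The text does not support that. It defines the intention-to-treat set separately and then describes a subset of its members.

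Three further objections have weight. The link between deviations and sodium is plausible but undocumented. Withdrawal below 130 mmol/L follows the protocol, so it is not clearly a deviation, and the illustration in step 4 depends on treating those children as lost. The figure of 17 might mean evaluable children, in which case the power losses in step 3 would not arise. Finally, a deviation-free analysis has a recognised place in an equality question. That supports keeping it beside the fuller set, but not making it the only set to which an analysis is assigned.

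**Conclusion.** The point holds in this form: as printed, the main comparison is assigned to a deviation-free subset formed after randomisation, in an open-label trial with an equality aim, and the count of three populations does not match what is described. This is a stated rule that needs correcting, not detail left to the analysis plan.

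Its effect on the estimate cannot be sized from the document. Bias can go either way. It would be going too far to say that the rule will produce a false finding of equality: the shrinkage from 5.0 to 3.35 mmol/L needs an assumed mean, normal values, SD 5 and the removal of every child below 130 mmol/L, none of which the document settles. The power figures of 0.81, 0.75 and 0.69 are correct for an unadjusted t-test, but the exclusions behind the last two are chosen for illustration.

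**What to change.** In *Analysis population*:

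1. State that the primary ANCOVA uses the set already defined there, all randomised children who received study fluid, analysed by allocated arm regardless of deviations.
2. State that children withdrawn for sodium below 130 mmol/L remain in this set, with their observed 24 h value or, where there is none, a value from the missing-data rule in the analysis plan. This concerns the analysis only and leaves the clinical withdrawal rule untouched.
3. Name the deviation-free set as per-protocol and make it supportive. Limit its exclusions to a list of major deviations fixed before data review, after reconciling the extra-fluid and replacement-of-losses statements.
4. Define the third population or change the count to two.

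Requiring both sets to agree before equality is claimed is an option for the sponsor and not a necessary part of the correction.

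The cost is a few sentences, one additional analysis run, and some effort to obtain or impute 24 h values for withdrawn children. Analysing the fuller set leaves the calculated 17 per arm unchanged.
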